#### Study parameter(s) intervention study

Frequencies, means and standard deviations will be used to describe the study variables. Differences between the study groups in baseline characteristics and clinical outcomes will be assessed and tested for statistical significance with the use of two-sided Fisher’s exact tests and chi-square tests for categorical variables and independent-samples t-tests for continuous variables. The primary study outcome measure of the intervention study is the change in the score on the SGRQ from baseline to 3 months: a paired *t*-test will be used to test the difference between the groups for statistical significance. Linear mixed models, with adjustment for baseline scores, will be used to study the effect of proactive palliative care on SGRQ outcomes during the follow-up period. The analysis follows the principle of intention to treat. Survival time will be calculated from the date of enrollment to the date of death with the use of the Kaplan-Meier method. A Cox proportional-hazard model will be used to assess the effect of proactive palliative care on survival, with adjustment for demographic characteristics.

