### Study design

The study consists of a controlled trial (assessment) with hospital as cluster, with a pre- and a post-test assessment. In total 6 hospitals will participate, 3 hospitals in the intervention condition and 3 hospitals in the control condition. Hospitals are selected for the intervention condition based on the presence of a specialized palliative care team. In the hospitals in the control condition standard care (usual care) will be delivered to patients with COPD by their treating lung specialists. In the hospitals in the intervention condition all patients with COPD will receive standard care by their treating lung specialist and those patients that are indicated for proactive palliative care by our set of indicators will also be supported by a specialized palliative care team on a regular base. Baseline measurements of the intervention study will be assessed from all participating patients during hospitalization for AECOPD before start of the intervention. Follow-up measurements will take place every three months, starting from the moment of discharge for a period of one year or until death. The primary outcome measure of the indicator study is time to death for any cause. The primary outcome measure of the intervention study is the change in quality of life measured by the St George Respiratory Questionnaire (SGRQ) at three month after baseline. As pre-test assessment, data will be obtained from the databases of the participating hospitals over a one year period preceding the assessment. These data on hospital-level are necessary to be able to compare hospitals at baseline. As post-test assessment, retrospectively the medical files of all participating patients will be examined over the assessment period. The assessment will take 18 month; 6 month for inclusion and 12 months for follow-up. The post-test assessment will be performed in the 3 months after the assessment.

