### Sample size calculation

The primary outcome in the intervention study is the quality of life of the patients measured with the SGRQ. More specifically the change in SGRQ three month after inclusion is the variable of interest. Koff et al. [51] published a difference in change of 9 between the two groups (standard care, standard care with proactive palliative care) with a common standard deviation of the change of 16. Then 64 patients would be needed in each group to obtain a power of 80% (two-sided *t*-test, alpha = 0.05). To adjust for the clustering at hospital level (ICC = 0.01, three hospitals per arm) and to allow for an additional loss to follow up of 10% a total of 86 patients are needed in each arm. This means that in each hospital 29 patients with an AECOPD are needed who have a poor prognosis according to our criteria. We expect to have to include between 60 and 90 patients with an AECOPD in each hospital to get sufficient patients that meet at least 2 criteria of the set of indicators.

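### The sample size allows for clustering by hospital, but the stated primary t-test and the t, Fisher and chi-square tests treat patients as independent, giving a type I error of about 8% at the protocol's own ICC

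*Protocol article*

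**What the plan says.** **Design.** Under Study design the protocol article states: "The study consists of a controlled trial (assessment) with hospital as cluster". It continues: "In total 6 hospitals will participate, 3 hospitals in the intervention condition and 3 hospitals in the control condition". The Randomization section adds that hospitals enter the intervention arm because they have a specialized palliative care team, so condition is a property of the hospital.

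**Sample size.** The Sample size calculation starts from a two-sided t-test at alpha 0.05: "Then 64 patients would be needed in each group to obtain a power of 80"%. It then enlarges this number: "To adjust for the clustering at hospital level (ICC = 0.01, three hospitals per arm"). With 10% loss to follow-up it reaches 86 patients per arm, or 29 per hospital.

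**Analysis.** Under Study parameter(s) intervention study:
- The primary outcome, change in SGRQ from baseline to 3 months, is compared between the groups with a t-test, which the text calls paired.
- Baseline characteristics and clinical outcomes are compared with Fisher's exact tests and "chi-square tests for categorical variables and independent-samples t-tests for continuous variables".
- For survival, "A Cox proportional-hazard model will be used to assess the effect of proactive palliative care on survival"; the only adjustment named is for demographics.
- Linear mixed models adjusted for baseline score are planned for SGRQ over follow-up. Their random effects are not given.

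**The concern.** Patients in one hospital share staff, case mix and care pathways, so their outcomes are correlated. The protocol accepts this when it enlarges the sample. A patient-level t, Fisher or chi-square test computes its standard error or reference distribution as if all patients were independent. If the ICC is above zero, that standard error is too small and the null hypothesis is rejected too often. Enlarging the sample does not cure this: it restores power for an analysis that respects the clusters, and the named tests do not.

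This is more than a detail left to an analysis plan. The article names the primary test, and that test conflicts with the article's own design and ICC. An analysis plan would have to overrule the stated test, not complete it.

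At stake is the error rate of the primary comparison and of the secondary comparisons made with the same kind of test.

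**Working it through.** **Inputs from the document:** 3 hospitals per arm; ICC 0.01; 64 per group before inflation; 10% loss; 86 per arm; SD of change 16; difference 9; two-sided alpha 0.05.

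**Assumptions made here:** equal hospital sizes; the primary test read as an ordinary two-group t-test, because a paired test cannot compare two separate groups; ICCs of 0.02 and 0.05 as a sensitivity range.

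**1. The plan's own inflation.**
- Hospital size m = 64/3 = 21.33.
- Design effect DE = 1 + (m − 1) × ICC = 1 + 20.33 × 0.01 = 1.203.
- 64 × 1.203 = 77.0, and 77.0/0.9 = 85.6, rounded up to 86.

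The stated 86 is reproduced, so the plan does treat hospital as a source of correlation.

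**2. Patients analysed per hospital.** 86 × 0.9 = 77.4 per arm, and 77.4/3 = 25.8, about 26.

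**3. Type I error of the patient-level t-test.** With DE = 1 + (25.8 − 1) × ICC, the true standard error is √DE times the one used. The real two-sided error is 2 × [1 − Φ(1.96/√DE)].

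| ICC | DE | √DE | Real error, formula | Real error, simulated (m = 26) |
|---|---|---|---|---|
| 0.01 (protocol) | 1.248 | 1.117 | 7.9% | 8.0% |
| 0.02 (assumed) | 1.496 | 1.223 | 10.9% | 10.8% |
| 0.05 (assumed) | 2.240 | 1.497 | 19.0% | 19.4% |

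The simulation used 60,000 runs with 3 against 3 hospitals. With 29 per hospital and ICC 0.01 it gave 8.3%.

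**4. The same result on the SGRQ scale, m = 26, ICC 0.01.**
- Standard error used by the test: √(2 × 16²/78) = 2.56 points.
- True standard error: variance of a hospital mean = 16² × (0.01 + 0.99/26) = 12.31; √(2 × 12.31/3) = 2.86 points.
- Ratio 2.86/2.56 = 1.12. Any 95% interval built on the smaller value would be about 11% too narrow (1 − 1/1.12).

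**5. A test that respects the clusters.** A t-test on six hospital means has 4 degrees of freedom and critical value 2.78. In simulation its type I error was 4.8% to 5.1% over all ICCs tried. Power from the noncentral t, m = 26:

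| Difference | Noncentrality at ICC 0.01 | Power, ICC 0.01 | Power, ICC 0.02 |
|---|---|---|---|
| 9 points | 9/2.864 = 3.14 | 66% | 58% |
| 8 points | 8/2.864 = 2.79 | 56% | 49% |

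The design-effect calculation with a normal approximation gives 88% for 9 points and 80% for 8 points at ICC 0.01. The gap arises because that calculation treats the between-hospital variance as known, whereas six hospitals give 4 degrees of freedom. The 8-point row is shown because 64 per group matches a standardised difference of 0.5, or 8/16. The stated 9 and 16 would need about 51 per group. That is a separate point.

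**The case against.** **The mixed models.** A reader might infer that every analysis in the section ignores hospital. The text does not support that. Linear mixed models exist to handle correlated data, and a condensed article may leave their random effects to the full protocol or analysis plan, so a hospital effect is neither stated nor ruled out. The same plan could add a frailty term or cluster-robust variance to the Cox model, although only demographic adjustment is named. Kaplan-Meier is named as an estimation method, not as a test. This objection stands and limits the point to the primary t-test and the t, Fisher and chi-square comparisons. It does not rescue the primary test, because the mixed models are described separately, for SGRQ over follow-up.

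**Size.** Only the 8% follows from the protocol's own ICC, and 0.01 is a planning value. If the true ICC were zero there would be no inflation. This also stands. At 0.01 the excess is moderate, and the 11% and 19% show sensitivity only.

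**Confounding.** A reader might also infer that accounting for hospital would stop a pre-existing difference between hospitals from being read as an effect of palliative care. It would not. Intervention hospitals were chosen for having a palliative care team. The protocol discloses this and plans a pre-test comparison of hospitals. A random hospital intercept handles random variation between hospitals, not a systematic difference between the two sets. The simulated 5% for hospital means assumes that hospitals are exchangeable between arms.

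**Conclusion.** The point holds for the stated primary test and for the t, Fisher and chi-square tests of clinical outcomes. As written they contradict a design that the same article calls clustered and sizes as clustered. At ICC 0.01 with about 26 analysed per hospital, the true standard error is about 12% larger than assumed and the two-sided type I error is about 8% instead of 5%. This rests on equal hospital sizes and on reading the paired t-test as a two-group t-test. The Cox model as described also names nothing for hospital. The mixed models are undetermined on this point. The analysis section mentions no confidence intervals, so the statement about their width applies only if intervals are reported from the same standard errors.

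**What to change.** - **Primary outcome.** Replace the t-test with a mixed model of SGRQ adjusted for baseline, with a random hospital intercept and small-sample degrees of freedom (Kenward-Roger or Satterthwaite). Alternatively, use a t-test on the six baseline-adjusted hospital means with 4 degrees of freedom.
- **Other comparisons between conditions.** State that the remaining continuous, binary and survival comparisons account for hospital, by a hospital-level analysis or by a hospital effect with a small-sample correction. State the random effects of the mixed models already planned.
- **Sample size section.** Restate the power for the cluster-respecting analysis.

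No new data are needed, but the cost goes beyond wording. Intervals become wider, and power with 4 degrees of freedom at ICC 0.01 is about 66% for 9 points and 56% for 8 points, below the 80% stated. The sponsor must either accept and report that power or reconsider the sample size or number of hospitals. The change corrects the stated uncertainty only. Confounding from the non-random selection of hospitals remains and needs its own treatment.

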### Randomization

Randomization will not take place. Hospitals will be selected for the intervention condition based on the presence of a specialized palliative care team in the hospital. In order to be able to compare the hospitals in the control- and the intervention condition a pre-test assessment will be performed.

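### The test named for the primary outcome, a paired t-test, cannot compare two unmatched groups of patients and does not match the two-group, clustered basis of the sample size

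*Protocol article*

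**What the plan says.** All references are to the protocol article.

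- **Statistical analysis, intervention study.** The primary outcome is defined: "The primary study outcome measure of the intervention study is the change in the score on the SGRQ from baseline to 3 months". The test follows directly: "a paired *t*-test will be used to test the difference between the groups for statistical significance".
- **Same paragraph, one sentence earlier.** Baseline characteristics and clinical outcomes are to be compared between study groups with "independent-samples t-tests for continuous variables".
- **Same paragraph, one sentence later.** A further analysis covers SGRQ over the whole follow-up: "Linear mixed models, with adjustment for baseline scores, will be used to study the effect of proactive palliative care on SGRQ outcomes". The sentence names no hospital term, and the model is not called the primary analysis.
- **Study design.** "In total 6 hospitals will participate, 3 hospitals in the intervention condition and 3 hospitals in the control condition".
- **Randomization.** There is none: "Hospitals will be selected for the intervention condition based on the presence of a specialized palliative care team in the hospital". No matching of hospitals or patients is described.
- **Sample size calculation.** A difference in change of 9 between two groups with a common SD of 16 leads to this statement: "Then 64 patients would be needed in each group to obtain a power of 80% (two-sided *t*-test, alpha = 0.05". The number is then raised for an ICC of 0.01 with three hospitals per arm and for 10% loss to follow-up, giving 86 per arm.

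**The concern.** A paired t-test needs a natural partner for each observation. Here the only natural pair is a patient's own baseline and 3-month scores, and a paired test on those asks whether one arm changed, not whether the arms changed differently. Across arms, pairs would have to be made up from unrelated patients in different hospitals.

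The timing of baseline makes this more than a matter of naming. Baseline questionnaires are completed during admission for an acute exacerbation, so some improvement by 3 months is plausible in both arms without any palliative care effect. A within-arm test would count that recovery as a result.

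The named test also leaves out hospital, although the sample size section allows for clustering by hospital. At stake is the p-value for the primary outcome of the intervention study.

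**Working it through.** **1. The plan's own figure.**
- Inputs: difference 9, SD 16, two-sided alpha 0.05, power 80%.
- An independent two-sample t-test needs 51 per group. A paired or one-sample t-test with SD of change 16 needs 27. Neither gives 64.
- An independent t-test at a standardised difference of 0.5 gives exactly 64.
- From 64 the next step reproduces: 64 × [1 + (64/3 − 1) × 0.01] / 0.9 = 64 × 1.2033 / 0.9 = 85.6, so 86 per arm and 29 per hospital.
- So the section describes a two-group, clustered comparison. That 64 does not follow from 9 and 16 is a separate point, and nothing below depends on it.

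**2. Does any pairing exist?** Study design and Randomization describe two sets of three hospitals, allocated by whether a palliative care team was present. Neither section sets up matched patients or hospitals. The only available pairs are within a patient.

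**3. What a within-arm paired test would do under no treatment effect.**
- Inputs: SD of change 16 (sample size section); 86 × 0.9 ≈ 77 analysed per arm; clustering left out for simplicity. The change common to both arms is an assumption, because the documents give no figure.
- Standard error of the mean change in one arm: 16/√77 = 1.82.

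| Assumed common change | Change / SE | One within-arm test significant | Independent t-test, patients independent |
|---|---|---|---|
| 0 points | 0 | 5% | 5% |
| 4 points | 2.19 | 58% | 5% |
| 9 points | 4.94 | over 99% | 5% |

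The chance that exactly one arm is significant is 2p(1 − p), where p is the within-arm figure. That is about 10% at 0 points, about 49% at 4 points and under 1% at 9 points. It peaks in the middle of the range, so no single value describes it.

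**4. Is a plain independent t-test enough?** With ICC 0.01 and 26 analysed per hospital, the design effect is 1 + 25 × 0.01 = 1.25. A test that ignores it has a true two-sided error of 2 × [1 − Φ(1.96/√1.25)] ≈ 8%; simulation gave 7.8%. Changing only the word "paired" therefore leaves an inflated type I error.

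**5. Power of a valid clustered comparison (difference 9, SD 16, ICC 0.01, 77 analysed per arm).**
- Design-effect calculation: 77 / [1 + (77/3 − 1) × 0.01] = 61.8 effective patients per arm. The standard error of the difference is 16 × √(2/61.8) = 2.88. Then 9/2.88 = 3.13, and power is Φ(3.13 − 1.96) ≈ 88%.
- Hospital-means t-test: the standard error is the same, but there are 6 − 2 = 4 degrees of freedom. Power falls to about 65% (simulation with 26 per hospital gave 66%).

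**The case against.** The strongest reply is that this is a slip of the pen. The sentence itself says that the test concerns the difference between the groups, the sample size is built on that difference, and the preceding sentence shows that the authors know the independent-samples test. That is the likeliest explanation, but it does not rescue the text. A test is named for the primary outcome and it is the wrong one, so a separate analysis plan does not excuse it. The obvious substitute, a plain independent t-test, would still ignore hospital.

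Two stronger readings should be resisted.

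- **That the trial has no valid test of its primary question.** A reader might infer this, but the documents do not support it. A baseline-adjusted mixed model is planned for SGRQ over follow-up, and Table 2 places SGRQ at 3 months within that period. Independent-samples tests are also planned for clinical outcomes. What is missing is their designation as the primary test, and a hospital term.
- **That the plan intends separate within-arm tests and will claim benefit if only the intervention arm is significant.** Nothing in the article says so. The percentages for within-arm tests show what would follow from one possible reading of the sentence. They also depend on a common recovery that the documents do not quantify.

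It is also fair to object that the hospitals are not randomised. If the arms differ at baseline, an analysis of change and an analysis adjusted for baseline can give different answers, so choosing between them is a decision of substance that must be stated.

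**Conclusion.** The point holds for the designated primary test. As written, that test cannot compare the two groups, conflicts with the two-group basis of the sample size, and omits the clustering allowed for there. The conclusion rests on the wording and the design alone and needs no numerical assumption.

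The size of the possible harm is conditional. If the test were run within arms, its rate of significant results under no treatment effect would range from 5% to over 99% across the assumed common change of 0 to 9 points. That calculation takes SD 16 and 77 analysed per arm. The wording should be corrected before the analysis, because it governs the primary outcome.

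**What to change.** Delete the paired t-test and name one primary analysis: the intervention-versus-control difference in SGRQ change from baseline to 3 months, estimated as the 3-month contrast of the linear mixed model already planned, with adjustment for baseline SGRQ. State three further things.

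1. A hospital term is added. It should be a random effect, because fixed hospital effects would absorb the condition effect.
2. A small-sample degrees-of-freedom correction for six hospitals is used, and which one.
3. Because allocation was not randomised, the between-group difference in change scores without baseline adjustment is reported as a sensitivity analysis, also allowing for hospital.

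The cost is a few sentences and no new data. The hospital term and the correction are new specifications, so power needs to be restated for the method chosen: for a difference of 9 with SD 16 it is about 88% on a design-effect calculation, but about 65% with a hospital-means t-test on 4 degrees of freedom.

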#### Outcome measures intervention study

1. The primary outcome measure is:

a. Change in quality of life (St George Respiratory Questionnaire (SGRQ) [36]) of the patient 3 months after inclusion

2. The secondary outcome measures are:

Patient-related

a. Change in quality of life (SGRQ) of the patient 6, 9 and 12 months after inclusion

b. Change in quality of life at the end of life (McGill Quality of Life questionnaire (McGill QOL) [37]) 3, 6, 9 and 12 months after inclusion

c. Change in psychological wellbeing (Hospital Anxiety and Depression Scale (HADS) [38]) 3, 6, 9 and 12 months after inclusion

d. Change in illness understanding 3, 6, 9 and 12 months after inclusion

e. Number and length of unexpected hospital admissions

f. Number and length of unexpected ICU admissions

g. Are the choices of Advance Care Planning (ACP) documented in the medical file? (when yes/when no)

h. Place of death (ICU/hospital/hospice/nursing home/at home)

i. Is preferred place of death known? (when yes/when no)

j. Has this wish come true? (when yes/when no)

k. Length of survival of COPD patients with proactive palliative care integrated with standard care versus standard care only

Informal caregiver-related

a. Change in informal caregiver burden (Self-Perceived Pressure from Informal Care questionnaire (SPPIC) [39]) 3, 6, 9 and 12 months after inclusion

b. Change in psychological wellbeing (HADS) at 3, 6, 9 and 12 months after inclusion

c. Change in illness understanding at 3, 6, 9 and 12 months after inclusion

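### The baseline-adjusted mixed model is named only for SGRQ; extending it to McGill QOL, HADS and SPPIC, collected on the same schedule, would gain precision and use incomplete follow-up

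*Protocol article*

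**What the plan says.** The protocol article, under Statistical analysis, Study parameter(s) intervention study, gives a general rule first: "Differences between the study groups in baseline characteristics and clinical outcomes will be assessed and tested for statistical significance". It assigns Fisher's exact and chi-square tests to categorical variables and "independent-samples t-tests for continuous variables". It then gives the test for the primary outcome, the SGRQ change at 3 months. The longitudinal method follows: "Linear mixed models, with adjustment for baseline scores, will be used to study the effect of proactive palliative care on SGRQ outcomes during the follow-up". SGRQ is the only scale mentioned in that sentence. The only other adjusted analysis in that section is the Cox model for survival.

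Under Outcome measures intervention study, the other scales are defined as change at the same four visits as SGRQ. Patient HADS is listed as "Change in psychological wellbeing (Hospital Anxiety and Depression Scale (HADS) [38]) 3, 6, 9 and 12 months after inclusion" and SPPIC as "Change in informal caregiver burden (Self-Perceived Pressure from Informal Care questionnaire (SPPIC) [39]) 3, 6, 9 and 12 months after inclusion". The McGill entry ends "McGill QOL) [37]) 3, 6, 9 and 12 months after inclusion". Caregiver HADS and the illness-understanding items, for patient and caregiver, are defined in the same way. Table 2 marks all of them at baseline, 3, 6, 9 and 12 months, exactly as it marks SGRQ.

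**The concern.** The plan has a suitable method for a repeatedly measured scale with a baseline value, and names it for one scale out of several that share a schedule. It gives no reason for the difference. If the general rule is applied to the others, each scale is compared by up to four separate tests. Each test leaves the baseline score unused as a covariate and takes only those who returned the form at that visit.

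Two things are at stake. The first is precision: a change-score comparison is noisier than a baseline-adjusted one. The second is incomplete follow-up: patients are followed for a year or until death, so some will have early visits but no late ones, and visit-by-visit tests make no use of the earlier forms at the later visits. SPPIC and caregiver HADS matter here because the intervention study's primary objective covers the wellbeing of informal caregivers as well as of patients.

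**Working it through.** **1. What the text assigns.**

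| Outcome | Time points (Table 2) | Method named in the analysis section |
|---|---|---|
| SGRQ | baseline, 3, 6, 9, 12 months | t-test on 3-month change; baseline-adjusted linear mixed model over follow-up |
| McGill QOL; HADS (patient, caregiver); SPPIC | the same | none by name; the general t-test rule if they count as continuous clinical outcomes |
| Illness understanding (yes/no items) | the same | none by name; the general Fisher or chi-square rule if they count as categorical clinical outcomes |

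The protocol states no precision or power for the scales other than SGRQ, so there is no figure of the plan's own to reproduce on this point.

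**2. Precision.** Let the variance at baseline and follow-up be equal (sigma squared) and let rho be their correlation.

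- Variance of a change score: 2(1 − rho) × sigma squared.
- Residual variance after baseline adjustment: (1 − rho²) × sigma squared.
- Ratio, adjusted to change: (1 − rho²) / [2(1 − rho)] = (1 + rho)/2.

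The document gives no rho, so 0.3 to 0.8 is an assumption. Clustering is ignored throughout.

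**3. The same result as power.** The sample size section asks for 86 patients per arm and allows for 10% loss: 86 × 0.9 = 77.4, so about 77 analysed. With 77 per arm and two-sided alpha 0.05 (two-sample noncentral t), a t-test on change has 80% power for a standardised difference of 0.454. Adjustment raises the effective standardised difference to 0.454 / √[(1 + rho)/2].

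| rho (assumed) | Variance ratio (1+rho)/2 | Extra variance of the change-score test | Effective difference | Power after adjustment |
|---|---|---|---|---|
| 0.3 | 0.65 | 54% | 0.564 | 94% |
| 0.5 | 0.75 | 33% | 0.525 | 90% |
| 0.7 | 0.85 | 18% | 0.493 | 86% |
| 0.8 | 0.90 | 11% | 0.479 | 84% |

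The 80% is only a reference point for comparing the two methods. The 77 is borrowed from the SGRQ calculation for patients.

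**4. Baseline differences between conditions.** Let D be the baseline difference between intervention and control hospitals, with no intervention effect.

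- If both conditions regress to a common mean, the expected follow-up difference is rho × D. The change comparison is then off by (1 − rho) × D in size (half of D at rho 0.5), and the adjusted comparison is centred on zero.
- If D is a stable difference between the hospitals' patients, the follow-up difference is again D. The change comparison is then centred on zero, and the adjusted one is off by D − rho × D = (1 − rho) × D.

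The error has the same size in both cases but falls on opposite methods. The document gives no information on which case applies.

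**The case against.** The strongest reply is that this argues from silence. The analysis section never names McGill QOL, HADS, SPPIC or illness understanding. The term clinical outcomes is not defined and could mean admissions, ICU days and place of death. The article is also a condensed account, and a full analysis plan may say more. This stands in part: the text does not say that these scales receive only t-tests. What remains is that the article states a method for continuous outcomes, names the better method for SGRQ alone, and gives the other scales the same schedule.

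A reader might infer that the t-tests let baseline differences between the selected hospitals bias the result. The documents do not support that as stated. The outcomes are defined as change, so a plain baseline difference is already subtracted. The remaining shift arises only if both conditions regress to a common mean. With hospitals chosen by presence of a palliative care team, a stable difference is just as possible, and then baseline adjustment is the method in error. Measuring baseline during an exacerbation does not settle this, because both conditions recruit during such an admission by the same procedure, so recovery common to both cancels.

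A reader might also infer that the illness-understanding items would be tested on follow-up answers alone. The section does not say this, and the outcome is defined as change.

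On the figures, rho is assumed, clustering is ignored, and 77 per arm does not describe caregivers, who consent separately, or later visits after deaths. At rho 0.8 the gain is about 4 percentage points of power. These limits bear on the size of the gain. Under the equal-variance model its direction is the same for every rho below 1.

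**Conclusion.** The point holds as a matter of precision and of using incomplete follow-up. For the scales on the SGRQ schedule, the model the plan already uses for SGRQ has 0.65 to 0.90 of the variance of a change-score t-test over an assumed rho of 0.3 to 0.8. A comparison with 80% power by t-test would have about 94% to 84% by the model. This rests on equal variances at baseline and follow-up, the assumed rho, about 77 analysed per arm, and no allowance for clustering. The use of partly observed follow-up is a further gain that these figures do not include.

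All the outcomes concerned are secondary, so the primary SGRQ comparison at 3 months is unaffected. No direction of bias is claimed.

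**What to change.** In Study parameter(s) intervention study, extend the mixed-model sentence from SGRQ to SGRQ, McGill QOL, HADS (patient and caregiver) and SPPIC. Use the baseline score as covariate and report the contrast between conditions at 3, 6, 9 and 12 months. State that the yes/no illness-understanding items are analysed with the logistic counterpart, including the baseline answer. If a fuller analysis plan already does this, the article's sentence should be aligned with it.

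The cost is one or two sentences and some programming, with no new data, visits or patients. The downside is that, with selected hospitals, baseline-adjusted and change-score results can differ, and neither removes hospital-level confounding. A change-score comparison can therefore be reported as a sensitivity analysis, with any disagreement shown openly.
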